## Abstract

**Background:**

Heart failure (HF) is one of the most serious health concerns worldwide. Anemia is a highly prevalent comorbidity and outcome predictor in HF patients. Sodium glucose co-transport 2 (SGLT2) inhibitors have been demonstrated to reduce the risk of cardiovascular death and HF hospitalization in HF patients.

**Purpose:**

This investigator-initiated, interventional, prospective, double-blind, multicenter study is designed to investigate whether anemia correction is one of the prerequisites and determinants related to the beneficial effects of dapagliflozin in HF patients.

**Methods and Results:**

Up to 2030 HF participants receiving standard care will be randomly assigned to either oral dapagliflozin 10 mg once daily or placebo 10 mg once daily for 12 months. The primary outcome is the composite incidence of hospital admission for HF and all-cause death. Secondary outcomes include change in the Kansas City Cardiomyopathy Questionnaire (KCCQ) score and change in 6-min walk distance and hemoglobin level. Patients will be followed for 12 months after randomization.

**Conclusions:**

The ADIDAS trial offers an opportunity to assess the hemoglobin change and association between hemoglobin change and readmissions due to heart failure and all-cause death in patients with heart failure treated with dapagliflozin or placebo. This study could highlight if dynamic hemoglobin change is related to the outcome for HF patients.

**Trial Registration:**

ClinicalTrials.gov; NCT04707261. Registration date, 2020/12/01, “retrospectively registered”

## Introduction

Heart failure (HF) is a severe clinical syndrome with high mortality and rehospitalization rate. The morbidity of HF is 1.5–2.0% in developed countries, and the rate is even more than 10% in people over 70 years old [1]. According to the epidemiological survey in 2003, the prevalence of heart failure in Chinese adults aged 35–74 was 0.9% [2]. It is estimated that its incidence will significantly rise within the near future.

In the 2017 ACC/AHA/HFSA Focused Update of the 2013 ACCF/AHA Guideline for the Management of Heart Failure, anemia, hypertension, and sleep-disordered breathing were listed as important comorbidities of heart failure [3], among which the incidence of anemia was 33.3% and the incidence of anemia was similar between patients with preserved left ventricular ejection fraction (LVEF) with HF (HFpEF) and reduced LVEF with HF (HFrEF) [4]. Moreover, anemia is independently associated with HF disease severity [3], poor functional capacity [5], hospitalizations, and mortality [4]. Clinical trials have demonstrated intravenous iron for the treatment of anemia improve exercise capacity and quality of life (QoL), but did not affect overall mortality [6, 7].

Dapagliflozin is a sodium-glucose co-transporter 2 inhibitor (SGLT2i). Recent clinical trials showed that dapagliflozin use was associated with significantly reduced HF hospitalization [8], worsening heart failure or death from cardiovascular causes [9], and increased HF-related health status [10]. The Dapagliflozin Effect on Cardiovascular Events trial (DECLARE–TIMI 58) showed 27% reduction in HF hospitalization in the dapagliflozin group [8]. In the Dapagliflozin And Prevention of Adverse-Outcomes in Heart Failure trial (DAPA-HF), the incidence of composite outcome with worsening heart failure or death from cardiovascular causes was 16.3% in the dapagliflozin group versus 21.2% in the placebo group (hazard ratio, 0.74; 95% confidence interval (CI), 0.65 to 0.85; *P*<0.001) [9]. DEFINE-HF trial (Dapagliflozin Effects on Biomarkers, Symptoms and Functional Status in Patients with HF with Reduced Ejection Fraction) also demonstrated a meaningful improvement in HF-related health status or natriuretic peptides [10]. In another trial, treatment with dapagliflozin resulted in correction and prevention of anemia in patients with T2D, and hemoconcentration due to a diuretic effect (early phase) and increased erythropoiesis (late phase) might be the underlying mechanisms responsible for these effects [11]. Though clinical trials have demonstrated that SGLT2 inhibitors have impressive beneficial cardiovascular effects in HF patients both with and without diabetes, the actual mechanisms still remain elusive. Several potential theses have been proposed, including modulation on ventricular loading, cardiac energetics, sodium-hydrogen exchange, erythropoietin, progenitor cells, and CaMKII [12]. Studies also found that SGLT2 inhibitors could upregulate SIRT1, then activate hypoxia-inducible factor-2α (HIF-2α) and hypoxia-inducible factor-1α (HIF-1α), which can promote erythropoietin synthesis, and might contribute to erythropoiesis [13–16].

Anemia correction belongs to a feature of effective strategies on HF [17]; it remains unknown if anemia correction is a prerequisite of dapagliflozin-induced beneficial effects in HF patients. Thus, in this randomized clinical trial, we tested the hypothesis that anemia correction is a major determinant related to the beneficial effects of dapagliflozin in patients with heart failure.

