## Methods

### Study Design

The primary objective of the ADIDAS trial (ClinicalTrials.gov Identifier: NCT04707261) is to investigate the hemoglobin change and the association between hemoglobin change and readmissions due to heart failure and all-cause death in patients with heart failure treated with dapagliflozin or placebo.

The study will include up to 12 sites within the Hunan Province, China, and up to 2030 participants receiving guideline recommended standard therapy will be computer-randomized to either oral dapagliflozin 10 mg once daily group or placebo 10 mg once daily group; the therapy duration is 12 months. Patients will be followed at 6 months and 1 year after randomization (Fig. 1).

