### Participant Selection

Patients aged ≥18 years with elevated NT-proBNP or BNP levels on admission, ejection fraction (EF) <50%, and New York Heart Association (NYHA) class II, III, or IV are eligible for enrollment. Exclusion criteria include patients who received treatment with SGLT2i during the past 3 months, or previous intolerance of an SGLT2 inhibitor, or severe (eGFR<30 mL/min/1.73 m^2 by CKD-EPI), unstable, or rapidly progressing renal disease at the time of randomization, pregnant, and breastfeeding women (Table 1).

**Table 1 Tab1:** Inclusion and exclusion criteria of the ADIDAS trial

Inclusion criteria ▪ Male or female between the ages of 18 and 100 years ▪ Elevated NT-proBNP or BNP levels on admission ▪ Ejection fraction of 50% or less, and New York Heart Association (NYHA) class II, III, or IV symptoms	
Exclusion criteria ▪ Treatment with SGLT2i during the past 3 months of admission, or previous intolerance of an SGLT2 inhibitor ▪ Severe (eGFR<30 mL/min/1.73 m^2 by CKD-EPI), unstable, or rapidly progressing renal disease at the time of randomization ▪ Pregnant or breastfeeding female patients	

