### Endpoints

The primary endpoint is a composite of hospital admissions for HF and all-cause death. Secondary endpoints include change in the Kansas City Cardiomyopathy Questionnaire (KCCQ) score and change in 6-min walk distance as well as hemoglobin level.

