Though clinical trials have evidenced that dapagliflozin have impressive beneficial cardiovascular effects in HF patients both with and without diabetes, the actual mechanisms still remain elusive. Numerous theories have been proposed to explain the beneficial effects of SGLT2 inhibitors; one of them is the increase of erythropoietin (EPO) levels. Study showed that SGLT2 inhibitors could raise the hematocrit [18], even in those without diabetes (as seen in DAPA-HF); it is speculated that these agents may promote erythropoiesis via enhanced EPO secretion by the kidney [19]. Mazer et al. [19] recently explored the impact of empagliflozin on EPO levels, red blood cell (RBC) morphology, and indices of iron stores in individuals with type 2 diabetes (T2D) and stable coronary artery disease (CAD). It was shown that EPO levels increased significantly after 1 month of empagliflozin treatment, and hematocrit increased after 6 months by 2.34% [95% CI 1.1, 3.57, *P*<0.001]. Studies also showed that SGLT2 inhibitors can stimulate SIRT1 and then activate hypoxia-inducible factor-2α (HIF-2α) and hypoxia-inducible factor-1α (HIF-1α), which can promote erythropoietin synthesis [13–16]. In another trial, dapagliflozin corrected anemia in 52% of patients with anemia at baseline (placebo: 26%), and the mechanism may be a combination of hemoconcentration due to a diuretic effect (early phase) and increased erythropoiesis (late phase) [11].

Anemia is a common comorbidity in patients with heart failure and associated with more severe symptoms and an adverse prognosis [3, 20]. Recent study suggested that dapagliflozin has beneficial effects on HF, and this effect might be related to the correction of anemia. A recent trial showed that intravenous iron replacement with ferric carboxymaltose reduced the risk of heart failure hospitalizations in patients with iron deficiency after an episode of acute heart failure [21]. SGLT2 inhibitors possess multiple mechanisms of improving HF syndrome, including correction of anemia; and our study aims to determine if elevation of hemoglobin is definitely linked with improved outcome in HF patients receiving placebo or dapagliflozin, if dapagliflozin use is associated with higher incidence of elevation of hemoglobin, and last but not least, if elevation of hemoglobin is accompanied by HF outcome improvement.

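### The hypothesis concerns anemia correction, but population, endpoints, primary objective and sample size concern hemoglobin and outcome in all HF patients; power among the anemic third is about 37%, not 80%

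*Protocol article*

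**What the plan says.** **The question.** The Abstract (Purpose) gives the aim as "to investigate whether anemia correction is one of the prerequisites and determinants related to the beneficial effects of dapagliflozin in HF patients". The Introduction repeats it as a hypothesis: "we tested the hypothesis that anemia correction is a major determinant related to the beneficial effects of dapagliflozin in patients with heart failure". The section Sample Size Determination and Statistical Analysis says that 1990 patients (995 per group) are needed to establish outcome benefits tied to anemia correction, with 80% power at two-sided 0.05.

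**The design.** The primary objective under Study Design is "to investigate the hemoglobin change and the association between hemoglobin change and readmissions due to heart failure and all-cause death", in HF patients on either treatment. Participant Selection and Table 1 admit adults with "elevated NT-proBNP or BNP levels on admission", an ejection fraction limit and NYHA class II to IV; none of the inclusion or exclusion criteria mentions hemoglobin or anemia. The primary endpoint is HF admission or all-cause death. The secondary endpoints are the change in KCCQ score and "change in 6-min walk distance as well as hemoglobin level". The closing aims in the Discussion speak of a rise in hemoglobin, with no restriction to anemic patients.

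**The share with anemia.** The Introduction reports for heart failure that "the incidence of anemia was 33.3" percent, similar with preserved and reduced ejection fraction.

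**The concern.** Anemia can be corrected only in a patient who has it. In a patient with normal hemoglobin a rise is a different event, and the Introduction itself attributes part of dapagliflozin's early hemoglobin effect to hemoconcentration from diuresis. If most of the cohort is not anemic, an association between hemoglobin change and outcome in everyone comes mostly from patients to whom the hypothesis does not apply.

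Two wrong conclusions then become possible. A whole-cohort association could be taken as support for anemia correction. Or an effect confined to anemic patients could be diluted and read as evidence against it. The sample size statement adds to this, because it suggests 80% power for the anemia-correction question when the calculation addresses another one.

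**Working it through.** **1. Reproduce the plan's figure.** Inputs from the sample size section: p1 = 0.212 (placebo), p2 = 0.163 (dapagliflozin), two-sided alpha 0.05, power 80%. Difference d = 0.049; mean p = 0.1875.

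n per group = [1.96 × √(2p(1 − p)) + 0.8416 × √(p1(1 − p1) + p2(1 − p2))]² / d²

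= [1.96 × 0.5520 + 0.8416 × 0.5509]² / 0.049² = (1.0819 + 0.4636)² / 0.002401 = 994.8, rounded up to **995 per group, 1990 in total**.

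This is an exact match. The plan adds 2% for dropout: 1990 × 1.02 = 2030. The calculation is the all-comer treatment contrast. Neither an anemic share nor a correction rate is among its inputs.

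**2. Patients with anemia to correct.** Assumption: the Introduction's 33.3% applies to the enrolled cohort.

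- Anemic: 2030 × 0.333 = 676, or 338 per arm.
- Not anemic: 2030 − 676 = 1354, or 66.7%.

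**3. Power for the treatment effect among anemic patients.** Assumption: the plan's event rates hold in that group.

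Power = Φ{[d√n − 1.96 × 0.5520] / 0.5509}

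With n = 338: [0.049 × 18.385 − 1.0819] / 0.5509 = −0.329, so power = **37%**. On the 1990 patients before dropout allowance (331 per arm) it is 36.5%. A Schoenfeld calculation at the cited hazard ratio of 0.74 gives 39% to 40%.

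**4. Range for the anemic share** (on 1990 patients):

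| Anemic share | Without anemia | Anemic per arm | Power in anemic patients |
|---|---|---|---|
| 20% | 80% | 199 | 24% |
| 25% | 75% | 249 | 29% |
| 33.3% | 66.7% | 331 | 37% |
| 40% | 60% | 398 | 42% |
| 50% | 50% | 498 | 51% |

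At no point in this range does power approach 80%. Reaching it among anemic patients at the same rates would take 1990 anemic patients, or about 1990 / 0.333 = 5976 all-comers.

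**The case against.** **The hypothesis can still be examined.** A reader might infer that the trial cannot answer its question. The documents do not support that. Study Visit and Follow-up provides for baseline laboratory measurements and hemoglobin checks at the visits, so baseline anemia and its correction can be derived once a threshold is set. Non-anemic patients are also informative: if the drug helps people with no anemia to correct, that counts against correction being a prerequisite. Enrolling them is not a fault, and an anemia-only trial would lose this evidence. This objection stands.

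**The analysis plan may supply the definitions.** The article says that all analyses will be detailed before database lock. A missing threshold or subgroup definition is therefore not in itself a finding. But an analysis plan would not change the wording of the hypothesis, the endpoint list, the primary objective or the purpose given for the 1990 patients, all of which are stated in this document.

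**The hypothesis is not refuted by the article's own figures.** The Discussion cites anemia correction in 52% on dapagliflozin against 26% on placebo in another trial. With 33.3% anemic, the drug-attributable corrections are 0.333 × 0.26 = 8.7% of the arm. Preventing every event in them at a 21.2% risk would yield 1.8 of the assumed 4.9 points. A reader might infer that correction is too rare to matter. That does not follow. The article calls it a major determinant and one of several mechanisms, not the whole effect. The result also reverses with other inputs: at 50% anemic and an assumed 40% risk, 0.50 × 0.26 × 0.40 = 5.2 points.

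**Misreporting is not announced.** The Abstract's Conclusions already speak only of hemoglobin change and need no rewording. The risk lies in the Purpose, the Introduction and the sample size section.

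**Conclusion.** The mismatch is real and should be corrected. The stated hypothesis is about anemia correction, while the population, endpoints, primary objective and sample size are about hemoglobin and outcome in all HF patients. About two thirds of the cohort (50% to 80%) would have no anemia to correct, so the whole-cohort association does not test the hypothesis. The 80% power belongs to the overall treatment contrast; among the roughly 676 anemic patients it is about 37% (24% to 51%).

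These sizes rest on two assumptions. The 33.3% is a background figure for heart failure and not an enrolment forecast, which is why a range is shown. The subgroup power uses the plan's overall event rates; higher event rates in anemic patients with the same relative effect would raise it. The overall randomized comparison of dapagliflozin with placebo is not affected.

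**What to change.** Leave eligibility and sample size as they are, and make four changes.

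1. Prespecify an anemia threshold on the visit 1 hemoglobin, and add anemia correction by randomized arm among baseline-anemic patients as a secondary endpoint.
2. Report the treatment effect on the primary composite, and the hemoglobin-outcome association, separately in baseline-anemic and non-anemic patients, with the treatment-by-baseline-anemia interaction. Item 1 alone shows only whether the drug corrects anemia; this item bears on whether correction matters for outcome and whether it is a prerequisite.
3. In the Abstract (Purpose) and the Introduction, call the whole-cohort quantity hemoglobin change, and limit anemia-correction conclusions to the analyses by baseline anemia.
4. Restate the sample size section so that 1990 patients and 80% power refer only to the overall dapagliflozin-placebo contrast.

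The cost is wording plus analysis of hemoglobin that is already to be measured; the article says enrolment has not started. The downside is precision. Anemia-correction results rest on about 676 patients, and the interaction is less precise still because it carries the sampling error of both subgroups. Both must be labelled accordingly.

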## Methods

### Study Design

The primary objective of the ADIDAS trial (ClinicalTrials.gov Identifier: NCT04707261) is to investigate the hemoglobin change and the association between hemoglobin change and readmissions due to heart failure and all-cause death in patients with heart failure treated with dapagliflozin or placebo.

The study will include up to 12 sites within the Hunan Province, China, and up to 2030 participants receiving guideline recommended standard therapy will be computer-randomized to either oral dapagliflozin 10 mg once daily group or placebo 10 mg once daily group; the therapy duration is 12 months. Patients will be followed at 6 months and 1 year after randomization (Fig. 1).

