### Sample Size Determination and Statistical Analysis

The ADIDAS study is powered on the event rates of previous large-scale study [9]. The incidence of composite outcome worsening heart failure or death from cardiovascular causes is 16.3% in the dapagliflozin group versus 21.2% in the placebo group (hazard ratio, 0.74; 95% confidence interval (CI), 0.65 to 0.85; *P*<0.001), as shown by DAPA-HF trial [9]. Thus, we estimated that with a total of 1990 patients (995 per group) required to determine the anemia correction-related beneficial effects on outcomes, the power of the study would be 80% with a 2-sided type I error rate of 0.05. Assuming that 2% of patients would withdraw or be lost to follow-up, the final sample size is determined to be 2030 patients (1015 per group).

All analyses will be detailed prior to database lock and unblinding. Summary tabulations will be presented for categorical variables, in which the number and percentage of participants within each category will be shown. As for continuous variables, the mean, median, standard deviation, first and third quartiles, and minimum and maximum values will be presented. The level of significance to be used for tests will be 0.05.

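### The stated primary objective (hemoglobin change and its association with outcome) has no matching primary endpoint, and the sample size powers a different comparison

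*Protocol article*

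**What the plan says.** Four parts of the protocol article bear on this.

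- **Objective (Study Design).** The primary objective "is to investigate the hemoglobin change and the association between hemoglobin change and readmissions due to heart failure and all-cause death", in patients treated with dapagliflozin or placebo.
- **Hypothesis and aims.** The Introduction puts it as a mechanism: "we tested the hypothesis that anemia correction is a major determinant related to the beneficial effects of dapagliflozin in patients with heart failure". The Purpose and Conclusions of the Abstract have the same focus. The Discussion lists three aims, all about a rise in hemoglobin; one is to learn "if dapagliflozin use is associated with higher incidence of elevation of hemoglobin".
- **Endpoints.** "The primary endpoint is a composite of hospital admissions for HF and all-cause death". The Abstract agrees: "The primary outcome is the composite incidence of hospital admission for HF and all-cause death". Hemoglobin appears among the secondary endpoints: "change in 6-min walk distance as well as hemoglobin level".
- **Sample size.** The inputs come from an earlier dapagliflozin trial in heart failure, where the incidence of its clinical composite "is 16.3% in the dapagliflozin group versus 21.2% in the placebo group (hazard ratio, 0.74; 95% confidence interval (CI), 0.65 to 0.85". The article then describes the result as "1990 patients (995 per group) required to determine the anemia correction-related beneficial effects on outcomes", with 80% power at a two-sided 0.05 level, raised to 2030 for 2% withdrawal or loss.

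**The concern.** The primary objective, the primary endpoint and the sample size should all concern the same question. Here the objective asks about hemoglobin and its relation to outcome, the endpoint measures a clinical composite, and the sample size text assigns the power for the second to the first.

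What is at stake is what the trial can validly conclude. A difference between arms on the composite is a randomized treatment effect, and it says nothing about whether a hemoglobin rise produced it. The association between hemoglobin change and outcome is a different kind of evidence. It sorts patients by something measured after randomization, so patients whose hemoglobin rises may differ in prognosis from those whose hemoglobin does not, in either arm. A reader who takes the sample size section at its word would believe that this second question has 80% power and the protection of randomization. It has neither.

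**Working it through.** **1. Reproduce the stated sample size.**

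Inputs, all from the sample size and randomization sections: p1 = 0.163, p2 = 0.212, two-sided alpha 0.05 (z = 1.960), power 80% (z = 0.842), allocation 1:1.

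For a two-proportion test with pooled variance under the null and no continuity correction:

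n per group = [1.960 × √(2 p̄(1 − p̄)) + 0.842 × √(p1(1 − p1) + p2(1 − p2))]² / (p2 − p1)²

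- p̄ = (0.163 + 0.212)/2 = 0.1875, so 2 × 0.1875 × 0.8125 = 0.3047, with square root 0.5520
- 0.163 × 0.837 + 0.212 × 0.788 = 0.1364 + 0.1671 = 0.3035, with square root 0.5509
- Numerator: (1.960 × 0.5520 + 0.842 × 0.5509)² = (1.0819 + 0.4636)² ≈ 2.389
- Denominator: 0.049² = 0.002401
- n = 2.389/0.002401 ≈ 994.8, rounded up to **995 per group, 1990 in total**

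This matches the article exactly, and the power at 995 per group is 80.0%. Other formulas come close without matching: 993 per group with unpooled variance or the arcsine method, and 1036 with continuity correction. An event-based calculation at a hazard ratio of 0.74 needs 347 events, or about 1851 patients in total at the mean rate of 18.75%. The allowance for loss is also reproduced: 1990 × 1.02 = 2029.8, given as 2030 (1990/0.98 = 2030.6).

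**2. Ask what that calculation tests.**

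Every input is an event proportion by arm, an error rate or the allocation ratio. There is no between-arm hemoglobin difference, no standard deviation of hemoglobin change, no proportion with anemia corrected and no measure of association between hemoglobin and outcome. The 80% is the power to detect a between-arm difference in a clinical composite. The article gives no figures from which power for the stated objective could be worked out.

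**3. Set objective against endpoint.**

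| Question | Where stated | Primary endpoint? | Powered? |
|---|---|---|---|
| Hemoglobin change | First half of primary objective; Discussion aims | No, secondary | No |
| Association of hemoglobin change with HF readmission and death | Second half of primary objective; Introduction; Discussion aims | No; the composite supplies the outcome, but the arm comparison does not test the association | No |
| Dapagliflozin versus placebo on the composite | Not stated as an objective | Yes | Yes, at the assumed rates |

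The one comparison that is randomized, primary and powered is the one that no objective spells out.

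**The case against.** The strongest defense is that the plan is less divided than it looks. The Abstract and the Endpoints section agree on a single primary endpoint. The sample size rests on a clinical composite. The objective names HF readmission and death as the outcomes, in patients on dapagliflozin or placebo, so the composite is part of the question. The article takes the drug's benefit as shown by earlier trials and asks about mechanism, which is a legitimate purpose.

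Much of this stands. The endpoint ranking is clear and consistent, and the composite does feed into the stated question. But this does not supply a primary endpoint or a power basis for the association, and it does not make the sample size sentence correct. Nor can the conflict be left to an analysis plan that is not shown, because the article itself states the objective, the endpoint ranking and the purpose of the sample size.

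A reader might go further and infer that the trial could be declared positive on hemoglobin alone, or that the investigators could choose between two definitions of success after unblinding. The documents do not support either. No section makes a hemoglobin result a criterion for success, and hemoglobin is explicitly secondary. The objective joins hemoglobin change to its association with outcome, so a hemoglobin difference alone would not meet it. The article also commits to detailing all analyses before database lock and unblinding. Nor can a probability of success on hemoglobin be set against the 5% error rate: the article gives no hemoglobin effect or standard deviation for this population, and detecting a real hemoglobin effect would not be a false positive.

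**Conclusion.** The concern holds as a mismatch between objective, endpoint and stated power. The primary objective has no corresponding primary endpoint, and the sample size sentence credits 80% power to a question that none of its inputs addresses. The arithmetic itself is right: 995 per group is exactly a two-proportion test of 16.3% versus 21.2%.

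The size of the problem is one of interpretation, and no numerical error is claimed. Even a significant primary result would leave the hypothesis in the Introduction untested, and the analysis that does address it would be a non-randomized comparison of unstated power. This rests on the wording of the article and the exact reproduction of its sample size, with no outside assumption. Whether the event rates borrowed from the earlier trial suit this trial's composite is a separate question and does not affect this point.

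**What to change.** 1. In Study Design, state the primary objective as the effect of randomized dapagliflozin versus placebo on the composite of HF admission and all-cause death over 12 months.
2. Make the between-arm comparison of hemoglobin change a secondary objective, in line with its present endpoint rank.
3. Make the association between hemoglobin change and outcome an explanatory, mechanistic objective, and say that it is a post-randomization comparison.
4. In the sample size section, say that the 80% power applies to the between-arm comparison of the composite only, and remove the attribution to anemia correction.
5. Bring the Purpose and Conclusions of the Abstract, the hypothesis in the Introduction and the aims in the Discussion into line.

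The article says enrollment has not started, so this is a change of wording with no effect on visits, data or sample size. The real cost is that the hemoglobin association can no longer be presented as the powered primary result. If the sponsor prefers to keep it primary, the alternative is to define an estimand for it and a sample size with its own inputs. That is more work and needs hemoglobin figures that the article does not give.
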